**Figure 1 F1:**
[figure not shown]
Study flowchart. fMRI, functional MRI.

#### Healthy controls

Thirty-six healthy controls will be primarily used for comparison of the results from the fMRI examination and the blood sampling. They will be matched at a group level in terms of gender, age and educational level. They will be recruited among hospital staff or their friends. For those who only undergo neuropsychological assessment and blood sampling, a token of Swedish krona (SEK) 300 will be offered and for those who do the fMRI and blood sampling, a token of SEK 1000 will be offered.

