**Trial registration number:**

NCT05452915.

Strengths and limitations of this studyA large cross-sectional multicentre study including 200 patients and 36 controls.Studying fatigue in chronic pain with objective neuropsychological measurements as well as biomarkers and brain imaging is an innovative approach to finding underlying pathophysiological mechanisms in this condition.The patients are consecutive clinical patients currently being evaluated for pain rehabilitation, which means that the results from the study are clinically generalisable.A study limitation is the small size of the control group; however, the size of the control group is adapted for comparison of the results from the functional MRI examination and blood sampling.

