### Participants

#### Patients for neuropsychological assessment

Two hundred outpatients between 18 and 50 years with CP from the Unit of Pain Rehabilitation at the Department of Rehabilitation Medicine at Danderyd University Hospital or from the Department of Pain Rehabilitation, Pain Center at Umeå University Hospital will be included. There will be no stratification of age, but the majority of the patients will be women as they are over-represented among those receiving rehabilitation for CP. In the analyses, the patients are compared with 36 healthy controls.

Please see the flowchart for an overview of the study (figure 1).

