#### Neuropsychological tests

WAIS-III Digit-Symbol-Coding (Coding) measures psychomotor speed and incidental memory. The higher values the better results.^61^ The Coding subtest from WAIS-III will be used instead of WAIS-IV as the former has been validated for measuring fatigability.^33 42^WAIS-IV Matrix reasoning measures logical reasoning and premorbid cognitive level. The higher values the better results.^62^WAIS-IV Digit Span measures verbal attention span and working memory. The higher values the better results.^63 64^Delis-Kaplan Executive Function Scale Color-Word Test and Word Fluency Test measure different aspects of executive functioning. For the Color-Word test, lower values represent better results and for the Word Fluency Test, higher values represent better results.^65^Ruff 2 & 7 measures automatic visual scanning and complex selective attention and processing speed. The higher values the better results.^66^MapCog Spectra is a newly developed attention test that is administered via an iPad. The MapCog test records and analyses the occurrence and frequency of attentional lapses and compares these to standardised norms. The standardisation is based on a healthy reference group, n=313, aged 8–87 years. The test has a sensitivity of 95.8% and a specificity of 96% for identifying individuals with attention deficit disorder. The test is easy to perform (5–10 min), the data processing is automatic, the results are objective and there are no learning effects. The lower values the better results.^67^ We also measure fatigability by comparing the results at the end of the test with the beginning of the test.

For all tests, mainly raw score scores will be used in the analysis.

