## Data collection and management

### Recruitment

The pain rehabilitation unit at the Department of Rehabilitation Medicine at Danderyd University Hospital and the Department of Pain Rehabilitation, Pain Center at Umeå University Hospital offer team assessment and evidence-based team-based multimodal rehabilitation for patients with complex CP (>3 months). To receive rehabilitation at the clinics, a referral including a pain assessment is required. Information about the study is sent to the referred patients at the same time as the call for the initial assessment.

At the time of the team assessment, the patient is asked orally by the team nurse if the testing psychologist may contact the patient to inform them about the study. The patient’s consent is logged, and a log is made of the number who say yes and the number and gender and age of those who say no. No personal data other than gender and age will be registered for those who say no. The purpose of the log is only to be able to assess generalisability based on the proportion who have agreed to participate in the study.

The testing psychologist then calls the patients and inform them about the study and if the patient agrees, an appointment is made for neuropsychological assessment. In connection with the assessment, the psychologist ensures that they have understood the information about the study and that participation is voluntary, inquires about whether they have further questions and collects the signed consent form. Female patients who are investigated in Umeå are asked if they want to participate in the fMRI study. The patients are assessed by an independent psychologist, who does not treat the patients clinically.

The study patients will be compared with healthy controls. Healthy controls will be recruited through advertising among hospital staff. Matching on a group level will be done regarding age, gender and level of education.

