### Data analysis

For all study questions, descriptive statistics will be used to depict demographics, injury characteristics, results on neuropsychological tests and psychological screening instruments. Multiple linear and logistic regression will be used to detect any interaction effects. Parametric methods such as independent t test, one-sample t test (comparing with standardised test norms), Pearson correlation and multiple linear regression) will be used when data are normally distributed and non-parametric methods (Man-Whitney U-test, Spearman correlation, χ^2^, logistic regression) when data are skewed or on interval level or lower. Missing data will be listed as data loss. The significance level will be set to <0.05 (two-tailed).

Concerning study question 4, data from omics and targeted analysis will be analysed using advanced MVDA using SIMCA-P+. This is the recommended method in omics since it accounts for multicollinearity problems and missing data when the number of variables exceeds the number of observations.^72^ MVDA will be used for the analysis of the biomarkers. Principal component analysis (PCA), orthogonal partial least squares- discriminant analysis (OPLS-DA) and OPLS regression will be applied for analysis of the biomarkers and their ability to differentiate between groups and their correlation with clinical characteristics and outcomes. PCA is an unsupervised analysis that reduces the dimensionality of data and extracts and displays systematic variation in the data matrix. Outliers will be identified using score plots in combination with Hotelling’s T2 test (the distance from the origin in the model plane for each selected observation) and DModX (the distance of the observation to the X model plane). The values that are larger than the 95% confidence limit are considered suspicious and the values larger than the 99% limit should be considered strong outliers.^73^

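### Question 1 compares 200 patients with 36 controls sized for the substudies, and neither the matching target nor any adjustment for age, sex, education or site is stated

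*Protocol article*

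**What the plan says.** The first question under Objectives asks whether patients with chronic pain have more self-rated mental fatigue and more cognitive fatigue than healthy controls.

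- **Patients.** "Two hundred outpatients between 18 and 50 years with CP from the Unit of Pain Rehabilitation" or from the Umeå centre are to be included. Age is not stratified, and most but not all patients are expected to be women. The same section states: "In the analyses, the patients are compared with 36 healthy controls".
- **Controls.** Under Healthy controls: "Thirty-six healthy controls will be primarily used for comparison of the results from the fMRI examination and the blood sampling". They are hospital staff or their friends. The strengths and limitations box adds that "the size of the control group is adapted for comparison of the results from the functional MRI examination and blood sampling". According to the Abstract and the section on fMRI participants, 22 of the 36 are women aged 18 to 45, chosen for comparison with fMRI patients who all come from Umeå.
- **Matching.** "They will be matched at a group level in terms of gender, age and educational level". Recruitment repeats this: "Matching on a group level will be done regarding age, gender and level of education". Neither sentence says whether the reference is the 200 patients, the 36 giving blood or the 24 scanned. Site is in neither list.
- **Scores and tests.** "For all tests, mainly raw score scores will be used in the analysis". Data analysis lists "Parametric methods such as independent t test, one-sample t test (comparing with standardised test norms), Pearson correlation and multiple linear regression", with Mann-Whitney, chi-square and logistic regression as the non-parametric set. The purpose it gives for multiple linear and logistic regression is to detect interaction effects.
- **Factors to control for.** The Abstract names pain-related factors, sleep disturbance and psychological well-being. The third question under Objectives names sleep disorders and depression or anxiety.

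**The concern.** The control group was sized for two substudies and then carried over to the full neuropsychological cohort. A group that resembles scanned women aged 18 to 45 from one site need not resemble 200 patients aged 18 to 50, of both sexes, from two sites. If the matching aimed at a subset, it gives no assurance for the whole cohort.

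Adjustment would be the second safeguard, but none is named for the demographic factors. An independent t test, Mann-Whitney or chi-square test takes no covariates, and a raw score, unlike an age-normed one, has no age correction built in. Any difference in age, sex, education or site that survives matching would enter the patient-control contrast. That contrast is the answer to question 1 for the Coding and Color-Word primary outcomes and for the self-rated fatigue scales.

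**Working it through.** **1. The plan's own figure.** The Sample size section gives a difference of 2.5, SD 3.0, two-sided alpha 5%, power 80% and 24 per group.

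- Normal approximation: n = 2 × (1.960 + 0.842)² × (3.0/2.5)² = 22.6, so 23 per group.
- t distribution: 23.6, so 24 per group, with power 80.7%.

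The stated 24 is reproduced.

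**2. Precision at 200 v 36.**

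- Standard error = √(1/200 + 1/36) = √0.03278 = 0.181 SD. With SD 3.0 this is 0.54 points.
- Power for a difference of 2.5 is 99.6%.
- The difference detectable with 80% power is 1.53 points.

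Precision is ample, so the weak point is validity. Adding patients shrinks the standard error but leaves a bias where it is.

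**3. Composition of the controls.** 22/36 = 61% are women aged 18 to 45. The article does not give the sex, age or site of the other 14.

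**4. What a residual imbalance would do (assumption).** The bias in SD units is the imbalance in a covariate (in its own SDs) times its correlation with the score. An imbalance of 0.25 SD with a correlation of 0.4 gives 0.10 SD. An imbalance of 0.5 SD with the same correlation gives 0.20 SD. None of these inputs is in the article.

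With no true pain effect, the rejection rate of a two-sided 5% t test follows from a noncentral t with noncentrality bias/standard error:

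| Assumed bias | Noncentrality, 200 v 36 | Error rate, 200 v 36 | Error rate, 36 v 36 |
|---|---|---|---|
| 0 | 0 | 5% | 5% |
| 0.10 SD (0.3 points) | 0.10/0.181 = 0.55 | 8.5% | 7.0% |
| 0.20 SD (0.6 points) | 0.20/0.181 = 1.10 | 19.6% | 13.3% |

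The points are on the SD of 3.0 used in the Sample size section. For the same bias the full cohort gives the higher error rate, because its standard error is smaller.

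**5. Factors against safeguards.**

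| Factor | Matched (group level) | Named as covariate |
|---|---|---|
| Age | yes, target not stated | no |
| Sex | yes, target not stated | no |
| Education | yes, target not stated | no |
| Site | no | no |

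**The case against.** The strongest reply is that three of the four factors are to be matched, and that the Recruitment section speaks of the study patients just before its matching sentence, which can be read as all 200. Most controls are women and so are most patients, so the known composition shows no mismatch. This stands. A reader might infer that demographic differences will be taken for a pain effect. The article supports only that they may be, because the matching target is ambiguous and group-level matching can leave a remainder.

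A reader might also infer that question 1 will be analysed without any adjustment. The article does not go that far. Its tests are a general list that includes regression, its control factors are introduced as examples, and a condensed article may leave covariates to a fuller document. What remains is that the article does name its tests, its score scale, the purpose of regression and its control factors, and that this set does not protect the contrast in question 1.

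Three further readings should be resisted.

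- The unequal group sizes do not themselves bias the estimate. Nor does the article say that the t test pools variances, so no error from that source can be charged to it.
- Comparison with test norms is not ruled out. The article says raw scores are used mainly, which leaves room for normed scores, and a raw score can be tested against a raw normative mean where one exists.
- Raw scores do not carry the full age effect into every outcome. Coding fatigability is a within-person difference and Color-Word uses contrast scores, and both remove at least part of a stable age or speed effect. The assumed correlation of 0.4 may be too high for them.

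Finally, the study calls itself explorative and acknowledges the small control group. That tempers the consequence, but the acknowledged limitation is the size of the group, not its comparability with the 200.

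**Conclusion.** The concern holds as a risk of residual confounding in question 1, not as a demonstrated bias. The article supports these facts: 36 controls sized for the substudies are compared with all 200 patients, the matching target is unnamed, site is neither matched nor named as a covariate, and no demographic covariate is named. The size is conditional: about 8.5% to 20% error instead of 5% if a bias of 0.1 to 0.2 SD survives matching, and 5% if none does. Which applies cannot be determined from the article. An adjusted analysis is nonetheless the better choice, because matching already requires age, sex and education to be known and power is not a constraint.

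**What to change.** - Make the primary analysis of question 1 a linear regression of score on group, age, sex and education, with standard errors robust to unequal variances. Use logistic regression with the same terms for the dichotomised Coding outcome.
- Add site only if controls come from both sites, which the article does not state. If they come from one site, say so and report site as an unadjusted limitation.
- Keep an unadjusted Welch test as a supportive analysis.
- Leave pain intensity out of the patient-control model. Healthy controls have essentially no pain, so the term cannot be separated from group. It belongs in the within-patient analyses.
- State the patient set to which the controls were matched, and tabulate age, sex, education and site for the 200 patients and the 36 controls.

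The cost is wording plus three model degrees of freedom, or four with site, among 236 participants. No new data on age, sex or education are needed. The Study setting section reports that data collection is complete but no analyses have been completed and reported, so the model can still be fixed in advance.

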#### Participants for fMRI

Twenty-four^24^ patients, women only, between 18 and 45 years with CP and who have undergone a neuropsychological assessment at the Department of Pain Rehabilitation, Pain Center at Umeå University Hospital will also undergo an fMRI investigation. All patients fulfilling the criteria for participation in the fMRI study from Umeå the study site are offered to participate in fMRI scanning and blood sampling, until the participation rate goal^24^ is reached. They will be compared with 22 female controls from the healthy control group.

#### Participants for blood sampling

Of the included participants, 36 patients and 36 controls will undergo blood sampling for immunological markers. All participants undergoing fMRI will also be eligible for blood sampling, as stated above. In addition, 14 patients from the Danderyd site will be consecutively recruited for the blood sampling part of the study.

### Eligibility criteria

#### Inclusion criteria

Disabling musculoskeletal pain for >3 months.Aged 18–50 years for neuropsychological assessment and 18–45 for fMRI examination.Referred to the Department of Rehabilitation Medicine at Danderyd University Hospital or to the Department of Pain Rehabilitation, Pain Center, Umeå University Hospital.

#### Exclusion criteria

Traumatic brain injury (including concussion).Extensive psychiatric problems or substance abuse.Previously congenital or acquired brain injury and/or does not live in their own home and who needs support in everyday life.Lack of knowledge of the Swedish language.Progressive disease.Drugs with a strong sedative effect.Pregnancy.For fMRI examination, patients with metal objects implanted in the body or metal chips in body parts (eg, after eye damage) are excluded. Patients are also excluded if they are afraid of confined spaces or if they are left handed.

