### Measurements

Background information from the Swedish Quality Register for Pain Rehabilitation (SQRP) (http://www.ucr.uu.se/nrs/). Information about medication, possible trauma and background information and degree of sick leave will be obtained from the medical record.

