### Blood sampling

Venous blood samples (10–20 mL) are collected in P100 tubes from BD diagnostic, containing a protease inhibitor cocktail that prevents protein cleavage/degradation from each subject. The blood samples are centrifuged to remove red blood cells. The plasma fraction is transferred to a new tube, portioned and stored at −86°C until analysis at the PAINOMICS lab in Linköping, Sweden.

Plasma samples will be analysed using antibody-based methods such as multiplex technology (Meso Scale Diagnostics, Rockville, MD). Instrument, MSD Technology platform, which is a multiplex instrument, which can analyse up to 92 different substances (cytokines, chemokines, growth factors and metabolic proteins) in one go. Omics analysis consisting of proteomics, metabolomics and lipoprotein profiling will be used to identify other inflammatory markers than those analysed by the antibody-based (targeted analysis) method.

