OPLS-DA will be used to identify biomarkers responsible for group separation. The OPLS-DA model reveals variables as loadings and the higher the value of a loading, the more important it is for the model, for example, group separation. This can be measured as a variable influence on projection (VIP) values. The p(corr) is the loading of each variable scaled as a correlation coefficient (ranging from −1 to +1). An absolute p(corr) of >0.4–0.5 and VIP >1.0 are considered significant.^72^ Another model diagnosis parameters that are considered are R2 value—which describes the ‘goodness of fit’, that is, the fraction of the sum of squares of all the variables explained by a principal component. The Q2 value describes the ‘goodness of prediction’, that is, the fraction of the total variation of the variables that can be predicted by a principal component using a cross-validation method^73^ and cross-validated analysis of variance (CV-ANOVA). The R2 must not differ more than 0.2–0.3 compared with Q2 and CV-ANOVA <0.05 is considered a significant model.

Regarding study question 5 analysis of fMRI data will be done with special software for MRI analysis, developed at Oxford University (http://www.fmrib.ox.ac.uk/fsl/). The resting state data will be analysed using FSL (http://www.fmrib.ox.ac.uk/fsl) tools such as MELODIC to identify spatial and temporal components by independent component analysis at the group level. All relevant preprocessing steps will be performed, such as motion correction, registration to a standard template and filtering of low-frequency drifts. Group differences between patients and controls will be analysed using FSL dual regression. The fMRI data will be analysed using both MELODIC and FEAT, which is an FSL tool based on general linear modelling performing multiple regression on the fMRI data and the functional paradigm.

For study question 6, multiple linear and logistic regression will be used to detect any interaction effects.

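### The patient–control OPLS-DA selects biomarkers without using recorded medication, so a selected marker could reflect drug treatment rather than chronic pain

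*Protocol article*

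**What the plan says.** All references are to the protocol article.

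- **Outcome.** Table 1 lists inflammatory markers as primary outcome 6 and calls the omics work mainly exploratory.
- **Who is compared.** Under Inclusion criteria, patients have "Disabling musculoskeletal pain for >3 months" and were referred to a specialist pain unit. Under Participants for blood sampling, "36 patients and 36 controls will undergo blood sampling for immunological markers". Of the controls, the Healthy controls section says "They will be matched at a group level in terms of gender, age and educational level".
- **Drug-related eligibility.** The Exclusion criteria name "Drugs with a strong sedative effect" and, separately, "Extensive psychiatric problems or substance abuse". Neither addresses ordinary use of anti-inflammatory or analgesic drugs. The blood-sampling sections add no drug restriction.
- **What is measured.** Under Blood sampling, a targeted panel of up to 92 substances is supplemented: "Omics analysis consisting of proteomics, metabolomics and lipoprotein profiling will be used to identify other inflammatory markers".
- **Medication data.** Under Measurements, "Information about medication, possible trauma and background information and degree of sick leave will be obtained from the medical record". The Abstract's list of controlled factors (pain, sleep, psychological well-being) and the covariates named in the Objectives do not include medication.
- **Selection rule.** Under Data analysis, "OPLS-DA will be used to identify biomarkers responsible for group separation". A variable counts as significant with an absolute p(corr) above 0.4–0.5 and VIP above 1.0. The model is judged by an R2–Q2 difference of no more than 0.2–0.3 and CV-ANOVA below 0.05. No covariate enters.
- **Timing.** Study setting states that data collection is complete and that no analyses have been completed and reported.

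**The concern.** Patients in specialist pain care are likely to take more anti-inflammatory and analgesic drugs than healthy controls. Such drugs can reach the data matrix in two ways: metabolomics may register the drug or its metabolites directly, and an anti-inflammatory drug may shift cytokine levels. OPLS-DA finds whatever distinguishes the groups and has no means of attributing a difference to pain rather than to its treatment.

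At stake is the meaning of the marker list for a primary outcome, which the Introduction hopes may lead to future diagnostic markers. The direction of any distortion is not fixed: drug-derived compounds can add spurious markers, while suppressed cytokines can hide real ones.

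This is more than detail left to a fuller document. The article gives the selection rule in full and names the confounders it will control. Medication is recorded but appears in neither.

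**Working it through.** **1. The plan's own figure.** The only computed sample size is 24 per group for WAIS-III Coding (difference 2.5, SD 3.0, two-sided 5%, 80% power). A t-test calculation gives 23.6, rounded up to 24, so it reproduces. The biomarker part has no calculation, and this point does not depend on the 24.

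**2. Association of drug use with group.** For equal groups with user proportions p1 (patients) and p0 (controls), and p̄ = (p1 + p0)/2, the correlation is φ = (p1 − p0) / (2√[p̄(1 − p̄)]). The article gives no drug use, so p1 = 30–50% and p0 = 5% are assumptions.

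| p1 | p0 | p̄ | φ |
|---|---|---|---|
| 0.30 | 0.05 | 0.175 | 0.25 / (2√0.1444) = 0.33 |
| 0.40 | 0.05 | 0.225 | 0.35 / (2√0.1744) = 0.42 |
| 0.50 | 0.05 | 0.275 | 0.45 / (2√0.1994) = 0.50 |

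This is a moderate association, of the same order as the 0.4–0.5 cut-off. The comparison is only indicative, because p(corr) is a correlation with the model score and not with group itself.

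**3. Do the model checks screen it out?** Simulation: 36 v 36, no disease effect, 3 variables driven by one drug, 5% use in controls, 7-fold cross-validation. The table gives the share of runs in which at least one drug variable met VIP > 1 and |p(corr)| > 0.4. Ranges are across separate runs of the same setting.

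| 200 noise variables, one orthogonal component | 40% of patients use | 50% | 60% |
|---|---|---|---|
| VIP and p(corr) only | 54–56% | 82–89% | 97–98% |
| and CV-ANOVA < 0.05 | 5–6% | 14–15% | 24–33% |
| and R2–Q2 gap ≤ 0.3 | 0% | 0% | 0% |

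If the 3 variables come from independent drugs, the CV-ANOVA row becomes 17%, 39% and 64%, and the gap row stays at 0%. With 20 noise variables and no orthogonal component, 46–96% of runs still pass both checks. The protection therefore comes from the amount of noise in the matrix, not from any recognition of drug effects.

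**4. Does using medication help?** A second simulation had 92 analytes, 10 of them shifted by 1 SD by drug use only, one predictive component, 5% use in controls and no CV-ANOVA. It gives the share of drug-only analytes selected at the 0.4 cut-off.

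| Patients using drug | Uncorrelated: ignoring drug → removing it | Correlated 0.3: ignoring drug → removing it | Q2 > 0 (uncorrelated / correlated) |
|---|---|---|---|
| 30% | 12% → 2% | 33% → 6% | 13% / 9% |
| 50% | 35% → 2% | 72% → 8% | 46% / 39% |
| 70% | 60% → 1% | 90% → 7% | 85% / 69% |

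With no drug use at all, selection is about 2% (uncorrelated) and 8% (correlated). Taking recorded use into account thus brings selection back to about the no-drug level. At 30% use, Q2 is mostly negative and the model would often be rejected. At 70% it is mostly positive.

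**The case against.** The strongest reply is that the plan does not accept a variable on VIP and p(corr) alone. A reader who saw only the top row of the first table might infer that the plan picks drug variables in more than half of studies. That does not follow: with many noise variables the plan's own checks cut the figure sharply, to zero under the R2–Q2 limit. This part stands, and those percentages should not be quoted as an error rate. It does not settle the matter, because the same checks let the drug signal through in a smaller matrix.

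A reader might also infer that drug use and group are almost collinear, so that no analysis could separate them. Correlations of 0.33–0.50 do not support that. At the assumed rates half or more of the patients are non-users, which is why a restricted repeat is feasible.

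The article is condensed, the work is labelled exploratory, and sensitivity models are often left to an analysis plan. Study question 4 itself asks about associations with cognition and fatigue, and the simulations address only the patient–control contrast. These points lower the weight. They do not remove the concern, because the selection rule is stated in full, its output serves a primary outcome, and group differentiation is part of the analysis described for question 4.

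The exclusion of strong sedatives may also remove some users of sedating analgesics, so not every analgesic user enters.

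**Conclusion.** The concern holds in a limited form. The stated patient–control OPLS-DA ignores medication, which is recorded and likely to be associated with group, so selected markers could reflect treatment rather than chronic pain. R2–Q2 and CV-ANOVA reduce the risk to an extent that depends on the numbers of variables and components. They do not test for it, because a genuine drug difference predicts group and can survive cross-validation.

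The size rests on assumed drug use (30–50% v 5%, correlation about 0.33–0.50) and on assumed drug effects. The article gives neither, nor does it say whether the metabolomics platform detects drug compounds. The claim that the results will be biased is therefore not supported; that they could be is.

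Nor is this a call to change eligibility. Data collection is over, and the remedy lies in the analysis.

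**What to change.** Add three steps to the biomarker part of Data analysis, before any results are examined:

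1. Remove features identified as drugs or drug metabolites from the metabolomics matrix before fitting PCA or OPLS-DA, and list them.
2. Repeat the patient–control OPLS-DA as a sensitivity analysis without patients recorded as using anti-inflammatory drugs, and without controls with such use where it is known. Describe a marker as pain-related only if its direction and approximate loading persist; otherwise describe it as possibly drug-related.
3. Within patients, check the selected markers against recorded anti-inflammatory and analgesic use, as a sensitivity analysis to the OPLS regressions.

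**Cost.** No new data are needed for patients. The repeat has fewer than 36 patients: at the assumed 30–50% use, about 36 × 0.70 = 25 down to 36 × 0.50 = 18. That is why step 2 asks for direction and approximate loading rather than a second pass of the thresholds. The marker list will probably be shorter.

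**Limits.** The record may miss over-the-counter use, so some confounding remains. The article states no medication source for controls and does not say that infection at sampling was recorded. The restriction on controls therefore applies only where use is known, and no restriction on infection is proposed.
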